### Milestones and products of pilot test

The primary goal of this project is to obtain pilot data for a large-scale clinical trial of different approaches to EBP adoption in healthcare. The research will be critical in developing (1) specifics of the guideline to be implemented, and (2) supports provided via the SCS implementation strategy and the systems consultants who deliver it. The protocol will be determined to be feasible if we enroll four intervention clinics, deliver the intended intervention in all four clinics, follow the clinics for a 6-month period, and obtain quantitative and qualitative data from participating clinicians. Acceptability will be gauged by assessing fidelity to the protocol and analysing qualitative data collected by the research team. We will continue to track effectiveness measures through the end of the 3-year grant period using de-identified electronic health records (e.g. opioid prescribing rate by clinician, number of treatment agreements signed) to assess the preliminary effectiveness of the SCS on clinical practice. With eight clinics reporting data (four intervention and four control clinics), we will be able to obtain baseline estimates of means and standard deviations for RE-AIM outcomes and point estimates of treatment effect sizes, thereby equipping us to conduct an accurate power calculation for the follow-up randomized trial.

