**Methods/Design:**

The pilot test will compare four intervention clinics to four control clinics in a matched-pairs design. A leading clinical guideline for opioid prescribing has been translated into a checklist-based implementation guide in a systematic process that involved experts who wrote the guideline in consultation with implementation experts and primary care physicians. Two physicians with expertise in family and addiction medicine are serving as the systems consultants. Each systems consultant will guide two intervention clinics, using two site visits and follow-up communication by phone and email, to implement the translated guideline. Mixed methods will be used to test the feasibility, acceptability, and preliminary effectiveness of the implementation strategy in an evaluation that meets standards for ‘fully developed use’ of the RE-AIM framework (Reach, Effectiveness, Adoption, Implementation, Maintenance). The clinic will be the primary unit of analysis.

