**Discussion:**

The systems consultation implementation strategy is intended to generalize to the adoption of other clinical guidelines. This pilot test is intended to prepare for a large randomized clinical trial that will test the strategy against other implementation strategies, such as audit/feedback and academic detailing, used to close the gap between knowledge and practice. The systems consultation approach has the potential to shorten the famously long time it takes to implement evidence-based practices and clinical guidelines in healthcare.

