### Rationale for proposed pilot study

This protocol was funded under the United States National Institute of Health’s R34 funding mechanism, the purpose of which is to “*provide support for the initial development of a clinical trial or research project*.” In this case, the funding will support a pilot study of the SCS to prepare for a large randomized control trial that will test the SCS against alternative approaches to EBP adoption in primary care. The SCS (1) teams clinical guideline writers with implementation specialists and primary care physicians to translate guidelines into a checklist-based implementation guide; (2) selects, trains, and deploys physician peer coaches (systems consultants) to help primary care clinicians implement EBPs using evidence-based tools of systems engineering; and (3) focuses on process as a cause of variation in outcomes. Although the SCS is rooted in established theory and empirical research, the approach has not been formally tested. This pilot test is intended to answer questions about the feasibility, acceptability, and preliminary effectiveness of the approach by studying adaptations that will be made to tailor the NIATx approach to primary care. In the future randomized trial, we will assess the costs and effects of the SCS versus other implementation strategies (such as audit/feedback or academic detailing) to determine the most cost-effective approach for reducing variation in opioid prescribing practices.

Primary care was chosen as the setting because, at a broad level, a strategy for improving the adoption of EBPs in primary care could apply to diverse patient populations and outcomes, and because primary care physicians are the main prescribers of opioids [13]. If clinical practice can be changed by simply informing physicians of their opioid prescribing levels and how they compare to peers, then audit/feedback may suffice to reduce variation in opioid prescribing. If education beyond audit/feedback is required, nurses or other healthcare professionals may deliver it relatively inexpensively through academic detailing visits. However, evidence from prior quality improvement research [1] and theory on organizational and individual change [14,15] suggests that changing clinical practice may require a more comprehensive strategy.

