### Clinic recruitment

Recruitment will focus on primary care clinics that are part of the DFMCH (n = 20). Clinics offering resident training will be excluded (n = 6); one clinic will be excluded from consideration because one of the systems consultants has an active clinical practice there. We selected the remaining 13 clinics as a recruitment pool to enable systematic monitoring of opioid prescribing rates and other clinical data through the clinical data warehouse housed by the DFMCH. The 13 clinics were first grouped into two categories (community vs. regional) and then ranked by the number of patients with long-term opioid prescriptions (defined as 10+ orders in the previous 12 months). Within these two categories, the clinics were paired by “nearest-neighbour” matching based on number of patients with 10+ opioid prescriptions. One pair of clinics will be recruited from the regional group (2/4 clinics eligible) and three pairs will be recruited from the community group (6/9 clinics eligible). Within each pairing, one clinic will be invited to be the intervention clinic by random selection. If that clinic agrees to participate (via a discussion between the systems consultant and the clinic’s medical director), the second clinic in the pairing will be assigned to the control condition. If the first clinic declines to participate, the second clinic in the pair will be invited to be the intervention clinic. If the second clinic agrees to participate, it will be assigned to be the intervention clinic and the first clinic will be assigned to control. If both clinics decline to participate, an alternate clinic will be selected within each category (there are three alternates among the community clinics and two alternate clinics in the regional clinics) until one of the alternate clinics agrees to participate.

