### Future directions

As outlined earlier, we intend to conduct a large-scale RCT to test the costs and effects of different approaches to EBP adoption in healthcare, including audit/feedback, academic detailing, and the SCS. We expect that some of the physicians who participate in this pilot research might themselves become systems consultants; indeed, 9 of the 17 coaches in the NIATx 200 study were former change leaders in addiction treatment clinics who went on to coach their peers.

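### The pilot's effect size is SCS versus control clinics, not the SCS-versus-active difference planned for the follow-up trial, so it cannot by itself support an accurate power calculation for that trial

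*Protocol article*

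**What the plan says.** **The pilot contrast.** The Methods/Design paragraph of the abstract says: "The pilot test will compare four intervention clinics to four control clinics in a matched-pairs design". Under Clinic recruitment, once the first clinic of a pair accepts, "the second clinic in the pairing will be assigned to the control condition". The article describes no activity for that condition. It also plans a before-and-after comparison within clinics, which again involves no alternative strategy.

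**The follow-up contrast.** It is described three times:
- The abstract's Discussion paragraph says the large trial will "test the strategy against other implementation strategies, such as audit/feedback and academic detailing".
- Rationale for proposed pilot study says: "we will assess the costs and effects of the SCS versus other implementation strategies (such as audit/feedback or academic detailing").
- Future directions says the large trial is to "test the costs and effects of different approaches to EBP adoption in healthcare, including audit/feedback, academic detailing, and the SCS".

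None of the three names a no-intervention arm.

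**The link between them.** Milestones and products of pilot test makes pilot data for the large trial the project's primary goal. It says the eight clinics will supply "baseline estimates of means and standard deviations for RE-AIM outcomes" and also "point estimates of treatment effect sizes, thereby equipping us to conduct an accurate power calculation for the follow-up randomized trial".

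**The concern.** A power calculation needs a target difference and a variance. The pilot's means and SDs do not depend on which comparator comes next. Its effect size does: it describes how far SCS moves outcomes relative to control clinics, whereas the planned trial asks how far SCS moves them relative to another strategy. If that other strategy has any benefit, the second difference is smaller than the first.

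This is a matter of comparator, separate from precision. With unlimited clinics and no sampling error, the pilot would still estimate SCS versus control. The article nevertheless presents the estimate as sufficient for an accurate calculation and mentions no discount. Because that calculation is a main product of the pilot, what is at stake is whether the next trial is sized for the question it is meant to answer.

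**Working it through.** **Is there a figure to reproduce?** No. The article gives no alpha, power, target difference, intraclass correlation or sample size for the follow-up trial, so the check is algebra plus an illustration on assumed inputs.

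**Step 1: relate the two contrasts.** Let D be the true effect of SCS versus control on some outcome, which the pilot estimates. Let the active comparator achieve a fraction f of D relative to the same control. Then

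SCS versus active = D - fD = D(1-f).

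**Step 2: effect on size.** For a two-arm comparison on the same scale, required size is proportional to 1/(difference)^2. Sizing on D when the truth is D(1-f) understates the requirement by the factor 1/(1-f)^2:
- f = 0: 1/1^2 = 1
- f = 0.25: 1/0.75^2 = 1.78
- f = 0.5: 1/0.5^2 = 4
- f = 0.75: 1/0.25^2 = 16

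**Step 3: effect on power.** Assumed inputs, none from the article: clinic as unit, 1:1 allocation, two-sided alpha 0.05, 80% power, normal approximation, and a standardised clinic-level effect d of 0.5 or 0.8 for SCS versus control.

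Clinics per arm: n = 2(1.960 + 0.842)^2/d^2. This gives 15.70/0.25 = 62.8, so 63, for d = 0.5, and 15.70/0.64 = 24.5, so 25, for d = 0.8.

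Power at that n when the true difference is d(1-f): Phi(d(1-f) x sqrt(n/2) - 1.960). For d = 0.5 and f = 0.25: 0.375 x sqrt(31.5) = 2.105, and Phi(0.145) = 0.558.

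| f | Power at 63/arm (d = 0.5) | Clinics/arm needed | Power at 25/arm (d = 0.8) | Clinics/arm needed |
|---|---|---|---|---|
| -0.25 | 94% | 41 | 94% | 16 |
| 0 | 80% | 63 | 81% | 25 |
| 0.25 | 56% | 112 | 56% | 44 |
| 0.5 | 29% | 252 | 29% | 99 |
| 0.75 | 10% | 1005 | 10% | 393 |

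The row f = -0.25 is a comparator that does worse than control; there the trial would be larger than necessary.

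**Step 4: precision, kept apart.** Treating the eight clinics as unpaired (6 df), an observed d of 0.8 has a 95% noncentral-t interval of about -0.68 to 2.23, and an observed d of 0.5 about -0.93 to 1.89. So the word *accurate* would be too strong even if the comparator were right. This error can move the sample size either way, and the comparator problem does not depend on it.

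**The case against.** The strongest reply is that the article never says the pilot estimate will be the target difference, undiscounted. It says the estimates equip the team for a calculation that has not been made, for a trial that has not been designed. That stands, and it limits the point in four ways.

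- **Certain underpowering.** A reader might infer that the follow-up trial is bound to be too small. The article does not support this: no sample size or target difference is stated, and the loss needs both undiscounted use and some benefit from the active strategies.
- **Untreated controls.** A reader might infer that control clinics receive nothing and only supply records. Some text leans that way: a clinic that declines the intervention becomes the control when its partner accepts, so control status appears to need no commitment. But the article speaks only of a control condition, and a condensed article may leave its content to the full protocol. The safe wording is control clinics with no described intervention.
- **A head-to-head difference near zero.** The Rationale section allows that audit/feedback could be enough, but only as a conditional. The same paragraph ends by expecting that a more comprehensive strategy may be required, and the Context section reports mixed results for these approaches. No value of f follows.
- **No untreated arm.** The comparator lists are open (*such as*, *including*), so a no-intervention arm is not excluded. If there were one, the pilot effect would inform that comparison, but still not the stated comparison with active strategies.

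The multiplier is also general algebra. It assumes a simple two-arm difference on a common scale, whereas the Rationale section frames the large trial around cost-effectiveness, which might be sized differently.

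Finally, the estimate should not be barred. SCS versus control, combined with outside evidence on active versus control, gives an indirect contrast: (SCS - control) - (active - control). That is a legitimate use, provided the uncertainty of both parts is carried through.

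None of this rescues the sentence as written. It claims a property that the pilot's contrast cannot supply, and nothing in the article qualifies it.

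**Conclusion.** The point holds in conditional form. The pilot estimates SCS versus control and the planned trial compares SCS with active strategies, so the claim that the pilot's point estimates will support an accurate power calculation for that trial is not justified. That conclusion rests on the article's text alone.

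The size of the consequence rests on assumptions. Used undiscounted, the pilot effect would leave a nominal 80% power at about 56%, 29% or 10% when the active strategies achieve 25%, 50% or 75% of the SCS effect, and would cost nothing if they achieve none of it. The article does not say which case applies.

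The pilot's allocation, measures, model and feasibility criteria are unaffected, and its means and SDs remain usable for planning whatever the comparator.

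**What to change.** Revise the last sentence of Milestones and products of pilot test as follows:

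1. Drop the word *accurate*.
2. State that the pilot effect estimate is SCS versus control and will not be used undiscounted as the target difference against active strategies.
3. Say that the pilot will supply means, SDs, between-clinic variance and feasibility data for planning.
4. Say that the target difference will be the smallest worthwhile advantage of SCS over the active comparator.
5. Allow the pilot effect to inform an indirect contrast, or the comparison with a no-intervention arm if the follow-up trial includes one.

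This changes wording only, with no change to clinics, data or analysis. The cost is a less favourable statement of what the pilot delivers.

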## Methods/Design

### Preliminary studies

In preparation for the grant submission, we analyzed preliminary data from the set of family medicine clinics that form the recruitment base for this pilot study. Substantial differences in opioid prescribing practices were evident. Clinics, and providers within clinics, varied substantially in the percentage of patients with three or more opioid prescriptions in the past year and average MEDD per patient. Compared with other patients, those with three or more opioid prescriptions more frequently reported smoking and drinking, were diagnosed more often with depression, and had substantially more clinic visits. Those in the highest MEDD group (4th quartile) had the least favourable profile. Of note, close to 50% of those in the 4th MEDD quartile reported regular alcohol consumption, which is discouraged in treatment agreements. These preliminary results align with evidence on the dose–response relation between MEDD and poor outcomes, [40] and further suggest that implementing universal precautions for opioid prescribing can reduce harms.

Specific Aim 1 consists of guideline translation and training of the systems consultants. Guideline translation has been conducted by the research team in consultation with the advisory panel. We followed a structured group decision-making approach called the integrative group process [41], a systematic technique for facilitating meetings of experts that incorporates the nominal group technique [28], the Delphi process [42], social judgment analysis [43], and cognitive mapping [44]. We began by conducting a structured Delphi process [28], in which we asked each member of the advisory panel to rate each recommendation in the opioid prescribing clinical guideline on its measurability, potential to reduce opioid abuse, and ease of implementation. We conducted follow-up telephone interviews with each panel member to understand the ratings they assigned. We compiled the results of the Delphi process to prioritize the panelists’ recommendations into a preliminary checklist.

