Specific Aim 3 uses mixed methods to understand how the strategy worked, including assessments of feasibility and acceptability (costs, ease of recruitment, fidelity to the protocol, physician acceptance) and preliminary effectiveness (degree of checklist implementation, effect of the strategy on variation in opioid prescribing rates and dosing levels). While multiple prescribers (primary care physicians, nurse practitioners, physician assistants) potentially practice within each clinic, the clinic will serve as the primary unit of analysis. Relevant comparisons for study measures will be made in two ways. First, historical data are available for many study measures, permitting time-series analysis of repeated measures to detect changes in a clinic over time (pre-intervention vs. post-intervention). Second, we can compare intervention and control clinics per the matched-pairs design.

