### Quantitative data collection and analysis

We will access many of our RE-AIM measures by tapping into clinics’ electronic health records via a data warehouse maintained in the DFMCH (e.g. reach data such as number and percentage of patients excluded, effectiveness and maintenance data such as overall rate of opioid prescribing by provider, etc.). The representativeness of the sample (patients, clinics, and staff) will be accessed through administrative databases maintained by the DFMCH. The quantitative analysis will focus primarily on patient-level opioid prescription rates measured in MEDD. Changes in outcomes will be assessed through repeated monthly observations. Data on prescribing will be augmented by other process and outcome measures shown in Table 1.

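### Standard deviations and effect estimates from four pairs of clinics cannot support a power calculation that the protocol calls accurate

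*Protocol article*

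**What the plan says.** The section on milestones and products of the pilot test gives pilot data for a large trial as the project's primary goal. It says the eight clinics will supply "baseline estimates of means and standard deviations for RE-AIM outcomes and point estimates of treatment effect sizes", and concludes "thereby equipping us to conduct an accurate power calculation for the follow-up randomized trial". No interval, sensitivity range or other data source is attached to that statement.

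The abstract fixes the design: "The pilot test will compare four intervention clinics to four control clinics in a matched-pairs design". The text on Specific Aim 3, under Clinic recruitment, adds that "the clinic will serve as the primary unit of analysis". Outcomes are followed monthly and analysed with a mixed model (Quantitative data collection and analysis; Statistical model).

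Two other places bear on the point. Under Preliminary studies the authors report that "we analyzed preliminary data from the set of family medicine clinics that form the recruitment base for this pilot study"; Clinic recruitment puts that pool at 13 clinics. The abstract's discussion, the rationale and Future directions all say that the follow-up trial will compare the strategy with other implementation strategies, such as audit/feedback and academic detailing. The Limitations section mentions secular trends but not the imprecision of these estimates.

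**The concern.** A trial that allocates clinics is sized on variation between clinics and on a target difference. The pilot would supply both from four pairs. Monthly patient-level records estimate within-clinic variation well, but they add no clinics. The between-clinic SD and the clinic-level effect therefore stay at a handful of degrees of freedom.

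Required size is proportional to the variance divided by the squared effect, so error in either input carries straight into the planned number. Inputs to the next trial are a stated product of this pilot. If its point estimates were used as they stand, the next trial could be far too small or needlessly large, and the word *accurate* would hide this from whoever plans it.

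There is a second, separate problem. The pilot measures the strategy against control clinics, whereas the next trial must detect a difference from active alternatives. Even a perfectly estimated pilot effect would be the wrong target.

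**Working it through.** The article gives no sample size, SD, effect, alpha or power, so there is no stated figure to reproduce.

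**Inputs from the article.** Four matched pairs, eight clinics, clinic as unit. Degrees of freedom: 4 − 1 = 3 (paired), 8 − 2 = 6 (pairing broken), 8 − 1 = 7 (one baseline SD over all eight clinics). The pool of 13 clinics would give 13 − 1 = 12.

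**Assumptions, because the article states none.** Two-sided 5%, 80% power, normally distributed clinic-level values, and a true effect of 0.3 to 1.0 SD of pair differences.

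**Step 1: the SD alone.** At a fixed target difference, true size / planned size = σ²/s². Its 95% limits are df/χ²(0.975) and df/χ²(0.025). The chance that true size exceeds ten times planned size is P(χ² < df/10).

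| df | χ² 2.5%, 97.5% | true / planned size | chance of more than tenfold too small |
|---|---|---|---|
| 3 | 0.216, 9.348 | 0.32 to 13.9 | 4.0% |
| 6 | 1.237, 14.449 | 0.42 to 4.85 | 0.4% |
| 7 | 1.690, 16.013 | 0.44 to 4.14 | 0.2% |
| 12 | 4.404, 23.337 | 0.51 to 2.72 | below 0.01% |

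Example at 6 df: with a target of 0.5 and an estimated SD of 1, the plan is 2 × (1.96 + 0.84)²/0.25 ≈ 63 clinics per arm, and the limits are 27 to 305.

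**Step 2: the effect estimate.** The 95% half-width is t(3, 0.975)/√4 = 3.182/2 = 1.59 SDs of the pair difference. Unpaired, it is t(6, 0.975) × √(2/4) = 2.447 × 0.707 = 1.73 between-clinic SDs. For a true effect of d SDs of pair differences, the mean of four pairs has standard error 0.5, so the chance of the wrong sign is Φ(−2d).

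**Step 3: both inputs from the pilot.** I simulated 200,000 four-pair pilots per scenario. Each right-sign pilot was sized for 80% power with its own effect and SD, and the true power was then evaluated.

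| true effect (SD of pair differences) | pairs needed | wrong sign | planned pairs, 10th to 90th percentile | true power below 50% |
|---|---|---|---|---|
| 0.3 | 90 | 27% | 6 to 644 | 59% |
| 0.5 | 34 | 16% | 5 to 301 | 46% |
| 1.0 | 10 | 2% | 4 to 48 | 27% |

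The last two columns are among right-sign pilots. At 1.0 SD the final figure is 29% if the normal formula replaces the t-based one. Counted over all pilots, the shares are 0.59 × 0.73 ≈ 43% at 0.3 SD and 0.27 × 0.98 ≈ 26% at 1.0 SD.

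**Step 4: chance of a size error above tenfold in either direction, both inputs estimated.** This counts wrong-sign pilots by the size of their estimate. For the paired analysis with a within-pair correlation of 0.5, where the SD of pair differences equals the clinic SD, it is 32%, 25% and 14% at effects of 0.3, 0.5 and 1.0 SD. Unpaired, in between-clinic SDs, it is 36%, 25% and 16%.

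**The case against.** The strongest reply is that the article commits to very little. It says the pilot *equips* the team for a power calculation. It does not say that the point estimates will be the only inputs, that intervals will be ignored or that historical data are ruled out. The next trial's sample size belongs in its own protocol. Effectiveness is repeatedly labelled preliminary, and no feasibility criterion uses an effect estimate. All of this stands. It limits the point to what the article asserts about accuracy, but it does not rescue that assertion.

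A reader might infer several stronger things that the documents do not support:

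- *That tenfold error is the norm at any of these degrees of freedom.* From the SD alone it has about a 4% chance at 3 df and 0.4% at 6 df. Beyond that it arises only when error in the effect is added.
- *That the next trial will most likely be underpowered, or that the interval exceeds any plausible effect.* The article states no plausible effect, and the simulated shares fall as the assumed effect rises.
- *That the strategy might be dropped on a chance result.* There is no go/no-go rule based on effect.
- *That moving from 3 to 12 df removes most of the risk.* The 3 df belong to pair differences under intervention and the 12 df to a baseline between-clinic SD. Historical data cannot show how much clinics vary in their response to the intervention. The preliminary analysis also reports only two prescribing measures, so not every outcome in Table 1 may be covered.
- *That the pilot is too small.* Four pairs suit its feasibility aims.

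**Conclusion.** The concern holds as a challenge to the claimed accuracy and to any reliance on the pilot's point estimates. The degrees of freedom follow directly from the design, and the SD limits in step 1 need no assumption beyond normality. At 3 df they leave the required size uncertain by a factor of about 43 from end to end (13.9/0.32), and at 6 df by about 12 (4.85/0.42).

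The wrong-sign and low-power figures depend on the assumed alpha, power and true effect. Across 0.3 to 1.0 SD they range widely, but even at the favourable end about a quarter of right-sign pilots would lead to a trial with less than 50% power. No part of that range fits the word *accurate*. The mismatch of comparators is independent of all these assumptions, and no other section of the article repairs the statement.

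**What to change.** In the milestones section:

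1. Replace *accurate* with *preliminary*.
2. Report pilot effects and SDs with confidence intervals, and state that the next trial will not be powered on the pilot's point estimate of effect.
3. Set that trial's target difference from the smallest effect worth detecting against its own comparators.
4. Supplement the pilot SDs with between-clinic variance, intraclass correlation and month-to-month correlation from the historical warehouse data of the 13 pool clinics, for the measures available there. Say plainly that these describe baseline variation, not variation in response to the intervention.
5. Plan on an upper confidence limit of the variance. A one-sided 80% limit, for example, multiplies the variance, and so the size, by 12/7.81 = 1.54 at 12 df, against 3/1.005 = 2.98 at 3 df.

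The cost is one paragraph and a query of data that the article describes as accessible. The downside is a less favourable claim and a larger planned size for the next trial. The pilot's size, recruitment, intervention, follow-up and feasibility criteria do not change.
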